### Recruitment {15}

All patients received hemodialysis in the center, excluding those who needed emergency care. There are between 17 and 34 punctures per day. Target sample sizes are not difficult to achieve.

## Assignment of interventions: allocation

### Sequence generation {16a}

We propose to match the 8 centers in their characteristics of number of patients and punctures per day.

The different experimental and control groups move forward in pairs.

There are 4 pairs, each comprising two centers. They are constituted in such a way that the 2 centers in each pair have similar characteristics, such as a comparable level of activity, a similar number of caregivers, particularly nurses, and a similar geographical environment in terms of urban and rural characteristics.

There were 4 centralized randomizations carried out by the Clinical Research Department of the Caen University Hospital. The TT group and the TTST group for each pair are already constituted. Consent, contrary to the Zelen method, is requested before randomization (Fig. 3).

**Fig. 3 Fig3:**
[figure not shown]
Randomization

### Concealment mechanism {16b}

All center managers gave their agreement to participate before the project began. Arm allocation for each pair is generated by a computer.

### Implementation {16c}

The pairs associating two centers were constituted by taking into account the level of activity, i.e., the number of dialysis patients managed and the number of caregivers present. The allocation of a pair in the group to the experimental group (or not) was done by computerized random draw. The randomization was conducted by the Clinical Research Department of the University Hospital Center of Caen. Four centers were in the control group, and 4 centers were in the experimental group.

To organize the training for each pair of centers, randomization was conducted by the Clinical Research Department of the University Hospital Center of Caen. Four centers were in the control group, and 4 centers were in the experimental group.

## Assignment of interventions: blinding

### Who will be blinded {17a}

N/A. Blinding is not possible in this study.

### Procedure for unblinding if needed {17b}

N/A. Blinding is not possible in this study.

## Data collection and management

### Plans for assessment and collection of outcomes {18a}

Data will be managed in a database administered by the sponsor. Data entry will be performed by the investigators at each center and may be performed by any person on the task delegation list. The system used for the computerized database will be in accordance with the regulations in force, particularly MR-01. Access to the database will be limited to authorized persons only (sponsor team, investigation team, principal investigator), and rights (read, write, specific pages of the case report form, patients of the center or all patients, etc.) will be assigned according to their role in the study and their center. Authentication of users will be assured by means of a username and a password personalized for each user. Connections to the database will be recorded in the connection history.

Consistency tests may be scheduled depending on the level of risk and/or impact of the study as defined by the sponsor. Following the execution of these tests, requests for clarification (queries) may be sent to the investigators to correct or confirm data entered in the database. Depending on the level of risk and/or impact of the study, a preanalysis committee may meet before the data are exported to qualify the deviations identified during the study and to decide whether or not to include the data collected in the study.

### Plans to promote participant retention and complete follow-up {18b}

Data are collected in the software used routinely in an e-case report form with the software EnnovClinical©.

### Data management {19}

Database development and administration are ensured by the North-West Canceropole Data Processing Centre (DPC) and under Caen University Hospital responsibility. Access is allowed to authorized people only through a highly secured system (VPN/SSL mode up to 128 bits; transmitted data encrypted). Its web interface allows study management via standard data entry in client/server and/or via the internet. Daily backup is made using two independent servers.

Data protection is based on (i) the definition of authorization profiles, defining the functions or types of information available to a user; (ii) control of access to the software by a username issued by the administrator and a password; (iii) electronic signature of the data; (iv) secure access to data by the “owner” only; (v) the audit trail that tracks all access, modification, and deletion of data; (vi) exported files archived within the system; (vii) all plotted transfers and uploads and downloads; and (viii) the possibility of automatic identification of patients without nominative data (creation of a unique patient identification number (alphanumeric) to enable interoperability of the data recorded and preserve anonymity).

Data quality is assured by pretesting and consistency checks during data entry. The software also includes a data management system of “queries.”

Storage: The Ennov Clinical© application is made available in SaaS mode by ENNOV™, which outsources its server installation and hosting services (software and data) to OVH™.

Backups are made daily (databases and servers). This is an incremental backup without overwriting data. A history is created allowing, if necessary, the recovery of previous data.

Data management/quality: The data processing center has quality procedures relating to Good Clinical Practice (GCP) guidelines and the use of the software. The DPC has been certified by the French National Cancer Institute (INCa) since July 2007 and International Organization for Standardization 9001:2015 since March 2018.

### Confidentiality {27}

Data collection is anonymous.

A number will be assigned to the nurses. This number will be known only to them. Neither the investigators nor other nurses will be aware of it. It will prevent any potential feelings of judgment or individual evaluation.

### Plans for collection, laboratory evaluation, and storage of biological specimens for genetic or molecular analysis in this trial/future use {33}

N/A. No biological specimens obtained during the conduct of the trial will be stored for future use.

## Statistical methods

### Statistical methods for primary and secondary outcomes {20a}

The difference in percentages between the two groups will be determined by a chi-square test, thus allowing us to meet the main objective. This result will be adjusted according to several criteria, two of them in particular: a center effect, a baseline effect, and an effect of the degree of experience of nurses.

Indeed, the analysis of cluster trials is more complex than the analysis of trials with individual randomization units. The analysis will therefore also be carried out at the cluster level using the guide of the French Health Authority of June 2007 (methodological guide downloadable from www.has-sante.fr).

The secondary objectives (number of per-dialytic bleeds, accidental needle withdrawals) will be analyzed according to the same procedures as for the primary objective. The pain score (numeric scale) at the time of puncture will be analyzed between the two groups by Student’s *t* test.

All the parameters collected will be analyzed.

Multivariate analyses will be considered according to the results of univariate analyses such as logistic regression comparing the two groups and mixed models.

The adjustments described above will also be applied to the secondary objectives.

The collection of the nurses’ feelings of expertise will be synthesized.

All analyses will be based on a first species error of 5% and will be two-tailed.

The IBM®-SPSS® data analysis software (IBM Corp. Released 2015. IBM SPSS Statistics for Windows, Version 23.0. Armonk, NY: IBM Corp.) will support all analyses.

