### Outcomes {12}

The primary outcome is the number of adverse events occurring during AVF puncture in the TT and TTST groups (comparison of percent occurrence of events in each group) defined by any of the following events: unipuncture failure, bipuncture failure, simple hematoma, hematoma not allowing continuation of dialysis.

The secondary outcomes are the number of perdialytic bleeds: accidental needle withdrawal, pain score (numerical scale) experience at the time of puncture, ease or difficulty of puncture, patients’ anxiety score (numerical scale) at the time of puncture, use of ultrasound by the nurse, and type of equipment used for the puncture (needle or catheter).

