### Sample size {14}

This is a comparative, prospective, multicenter evaluation study taking place in 8 centers. The population is made up of all nurses performing hemodialysis punctures. We expect a reduction of at least 50% of the complications related to the puncture in the experimental group compared to the control group (possible result following the first pilot feasibility study, monocentric, prospective, observational, before/after, SIMFAV (RCT03680209) carried out at the University Hospital of Caen Normandy). To show a significant difference at T8, a minimum of 1 complication per day (the least favorable condition for confirming our hypothesis) was considered, i.e., over 4 weeks and for 8 centers, 224 complications in the control group, or 9.3%. For a reduction of at least 50% (4.65%), a risk *α* equal to 5%, and a power of 90%, it is necessary to have a total of 610 punctures, i.e., approximately 80 per institution. The randomization of hospitals and not of caregivers (registered nurse) allows us to avoid the risk of contamination between the two groups and to simplify the organization of the study within each institution. The Hawthorne effect should be reduced by the fact that, at the end of the study, the TT group will benefit in the same way as the TTST group from the procedural and hybrid simulation training. This should ensure that all the caregivers will adhere to the project and thus be motivated to do so in a perfectly equitable manner. The methodology of randomizing hospitals and not caregivers, the so-called cluster approach, leads to caregivers in the same cluster being more similar (intraclass/intracluster correlation, ICC) than caregivers from different institutions randomized globally. To correct for this impact on variance, it is necessary to apply a variance inflation correction factor equal to (1 + (*m*-1) *r*) to the required number of subjects, with *m* equal to the realized number of punctures within a cluster and *r* being the ICC. The value of *r* can be relatively high because of the way in which a facility or department performs its nursing practice. To be able to carry out all the analyses and to take into account additional analyses (center effect, effect of the number of punctures performed and the degree of experience of the nurse, etc.), and feasibility, the highest number of 600 punctures per center, i.e., 4800 punctures, 2400 per group, is used. This number of 600 punctures per center takes into account the number of establishments.

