
The same number of 4800 punctures for the T5 period (baseline) is also used. This means a total of 9600 punctures over the study period.

Several levels are taken into consideration: center, nurse, patient, and AVF puncture. Within a single center, the overall reflection of activity is related to history, practices, schedules, recommendations, etc. This center-specific activity may differ from one center to another. The experience of the nurses led to the same effects from one center to another, such as the characteristics of the patients and the AVF. These different points are taken into consideration to look for possible differences and effects that could be the cause of confounding factors.

In total, 8 centers participated, with 600 pretraining punctures per center and 600 posttraining punctures per center; that is, 9600 punctures were observed.

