### Methods for additional analyses (e.g., subgroup analyses) {20b}

The difference in percentages between the two groups will be determined by a chi-square test, thus allowing the main objective to be met. This result will be adjusted according to several criteria, in particular two of them: a center effect, a baseline effect, and an effect of the degree of experience of the nurse.

Indeed, the analysis of cluster trials is more complex than the analysis of trials with individual randomization units. The analysis will therefore also be performed at the cluster level using the Health French Authority of June 2007 cluster (methodological guide downloadable from www.has-sante.fr).

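### The test tied to the main objective is a puncture-level chi-square, although eight centers are randomised; its 5% level fails for any positive ICC, and no rule lets another planned analysis decide

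*Protocol article*

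**What the plan says.** Centers are the unit of randomisation: four matched pairs, four centers per arm (Protocol article, sections {8}, {16a} and {16c}). The primary outcome is a "comparison of percent occurrence of events in each group" (section {12}), with 600 post-training punctures per center and 2400 per group (section {14}).

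For the test, section {20a} states: "The difference in percentages between the two groups will be determined by a chi-square test, thus allowing us to meet the main objective". Section {20b} says the same: "The difference in percentages between the two groups will be determined by a chi-square test, thus allowing the main objective to be met". The error rate is also fixed: "All analyses will be based on a first species error of 5% and will be two-tailed".

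The article does recognise clustering. Section {14} explains that randomising hospitals "leads to caregivers in the same cluster being more similar", gives the inflation factor 1 + (m − 1)r, and says r may be fairly high, without giving it a value. It adds: "Several levels are taken into consideration: center, nurse, patient, and AVF puncture".

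Sections {20a} and {20b} then say that the result will be adjusted for center, baseline and nurse experience, and that an analysis will also be done at cluster level following a French Health Authority guide. Section {20a} adds that multivariate analyses, mixed models among them, will be considered in the light of the univariate results.

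For pain, section {20a} says "The pain score (numeric scale) at the time of puncture will be analyzed between the two groups" by Student's t test, and extends the adjustments to the secondary objectives.

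**The concern.** A Pearson chi-square on pooled punctures assumes that every puncture is an independent observation. Here punctures are nested in patients, nurses and centers, and only eight centers were allocated. The variance of the difference in percentages therefore includes between-center variation, which the chi-square leaves out. The sample-size section says this inflation has to be applied; the named test does not apply it.

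At stake is the main conclusion. If four centers happen to differ from the other four for reasons unrelated to the training, the chi-square can call that difference significant. Because several analyses are listed and none is given precedence over the one linked to the main objective, a significant chi-square could be reported as the trial's answer even when a center-level analysis disagrees.

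**Working it through.** **Inputs from the article.** Four centers per arm; m = 600 punctures per center; 2400 per arm; two-sided 5%; 90% power; event rates 9.3% and 4.65%; inflation factor 1 + (m − 1)r. **Assumed:** the ICC r, shown from 0.001 to 0.05 because the article gives no value.

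**The plan's own figures.** Section {14} gives "224 complications in the control group, or 9.3" per cent, and 224/2400 = 9.3%. (The 224 is 28 days × 8 centers, whereas the control group has four.) The unclustered requirement of 610 punctures in total does not reproduce: the two-sided pooled formula for 9.3% versus 4.65% at 90% power gives 629 per arm, or 1258 in total. These are separate matters. The error-rate formula below does not involve the event rate; the power figures take 9.3% and 4.65% at face value.

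**Type I error of the chi-square.** With design effect DE = 1 + 599r, the true standard error is √DE times the one the test uses, so

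error = 2 × [1 − Φ(1.96/√DE)].

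For r = 0.01: DE = 1 + 5.99 = 6.99; √6.99 = 2.64; 1.96/2.64 = 0.74; error = 46%.

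| ICC | DE | Effective n per arm (2400/DE) | Error, formula | Error, simulation |
|---|---|---|---|---|
| 0.001 | 1.6 | 1501 | 12% | 12% |
| 0.005 | 4.0 | 601 | 33% | 32% |
| 0.01 | 7.0 | 343 | 46% | 46% |
| 0.02 | 13.0 | 185 | 59% | 58% |
| 0.05 | 31.0 | 78 | 72% | 73% |

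The simulation used a beta-binomial model: 40,000 trials, 4 versus 4 centers, 600 punctures each, rate 9.3%. At ICC 0 the chi-square rejected in 4.8%, so the excess comes from clustering alone.

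**Credit for matching.** If pairing removed half of the between-center variance, DE = 1 + 599 × r × 0.5:
- r = 0.001: DE = 1.30, error about 9%
- r = 0.01: DE = 4.0, error about 33%
- r = 0.05: DE = 16.0, error about 62%

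**A center-level test on the same simulated data.** The t test on eight center percentages (6 df) rejected in 4.6% to 5.0% over the tabulated ICCs. Power for 9.3% versus 4.65%, using post-training data only:

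| ICC | t test, 6 df | Paired t test, 3 df (no gain from matching assumed) |
|---|---|---|
| 0.001 | 98.5% | 90% |
| 0.005 | 76% | 58% |
| 0.01 | 53% | 38% |
| 0.02 | 33% | 24% |
| 0.05 | 17% | 12% |

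**Do the other planned analyses repair the primary test?**
- *Center adjustment:* no model is stated. In post-training data each center sits in one arm only, so a fixed center effect is aliased with arm. The baseline period could help identify an effect, but the article does not say how, or how center variation enters the standard error.
- *Cluster-level analysis:* it is planned in addition, specified only by citing a guide, with no rule that it decides.
- *Mixed models:* they depend on univariate results, so they are not a commitment.

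**The case against.** The strongest reply is that the plan does not overlook clustering. The sentence after the chi-square promises adjustment for center, baseline and nurse experience. The next paragraph presents the cluster-level analysis as the consequence of the cluster design, and nothing formally ranks it below the chi-square. The adjustments extend to pain. The centers were matched, which lowers the excess error. An analysis plan that is not shown may settle the model.

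Much of this is right, and it limits what can be said. A reader might infer that the trial disregards randomisation by center altogether; the document does not support that, because it plans further analyses that address it. A reader might also infer that the cluster-level analysis has been declared secondary; it has not been ranked at all. And a reader might charge that the primary confidence interval is too narrow; sections {20a} and {20b} plan no interval for this test, so the charge belongs to the p-value. An interval built on the same independence assumption would be too narrow, but none is described.

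What the reply does not remove is that two sections attach the main objective to the chi-square and no text lets another result override it. An analysis plan would have to contradict this wording, not just fill it in. For pain, extending an adjustment without a stated model does not clearly cure the t test.

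**Conclusion.** The point holds for the named test and for the lack of a deciding rule. The chi-square does not keep the stated 5% level for any ICC above zero. How far it misses depends on an ICC that the article does not give. Without credit for matching, the error runs from about 12% at ICC 0.001 to about 72% at 0.05. If matching removes half of the between-center variance, it is about 9%, 33% and 62% at 0.001, 0.01 and 0.05.

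It would be tempting to say without condition that 5% is far exceeded. The documents do not support that: at ICC 0.001 with effective matching the excess is modest, though the article itself expects r could be fairly high. The calculation covers correlation within centers only; repeated punctures by the same nurse or in the same patient are likewise left out by the chi-square. The Student's t test on pain has the same fault.

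**What to change.** Before analysis, name one center-level analysis as the sole primary. For example: for each center, take the post-training minus the baseline log-odds of an event, compare the arms by a t test on 6 df, and report the matching t-based 95% CI. State that this result decides the main objective. Keep the pair-matched version (3 df), or a mixed model with a random center effect and small-sample correction, as a sensitivity analysis, and the chi-square as description only. Analyse pain by center-level means in the same way. A within-pair permutation test should not stand alone: with four pairs its smallest two-sided p-value is 2/16 = 0.125.

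The change itself is wording; no further data are needed. The cost is power. Against the 90% in section {14}, a post-training-only center-level t test has about 76% at ICC 0.005, 53% at 0.01 and 33% at 0.02. Using the baseline may recover some of this if center differences are stable over time, and may lose some if they are not. The power statement should be restated for the center-level test, with the assumed ICC given.

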## Trial design {8}

This is a prospective, multicenter cluster randomized controlled trial.

All centers use the same types of medical devices (catheters and puncture needles) and have an ultrasound machine available on site. The number of daily punctures varies from 13 to 40 depending on the center. A center effect will be sought.

Only two centers have a lower number of patients and punctures, but they are still comparable. We therefore propose to match the centers according to number of patients and punctures per day. We grouped the centers into pairs according to the criteria of number of AVF punctures per day, number of nurses, before randomization.

The different experimental and control groups will move forward in pairs (e.g., center A of the experimental group, center A of the control group).

The trial design is described in Fig. 1.

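### The primary chi-square result is to be adjusted for centre, which is nested in arm, with no fixed model saying how; make one centre-level analysis decisive

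*Protocol article*

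**What the plan says.** **Design.** Trial design {8}: "This is a prospective, multicenter cluster randomized controlled trial". Implementation {16c}: "Four centers were in the control group, and 4 centers were in the experimental group". Sequence generation {16a}: "There are 4 pairs, each comprising two centers" and "There were 4 centralized randomizations carried out by the Clinical Research Department of the Caen University Hospital", that is, one draw per pair.

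**Data.** Sample size {14} plans 600 post-training punctures per centre, 4800 in all, and adds: "The same number of 4800 punctures for the T5 period (baseline) is also used". Every centre therefore has a before and an after sample. No numerical ICC is given, but the section says it may be fairly high.

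**Analysis.** Statistical methods {20a} assigns the main objective to a chi-square test on the two groups' percentages. It then says: "This result will be adjusted according to several criteria, two of them in particular: a center effect, a baseline effect", with nurse experience as a third item (the sentence announces two). Methods for additional analyses {20b} repeats this almost word for word. Both sections add a cluster-level analysis by reference to an outside guide. On models, {20a} says: "Multivariate analyses will be considered according to the results of univariate analyses", giving logistic regression and mixed models as examples. Trial design {8} adds: "A center effect will be sought". Neither analysis section mentions the pairs.

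**The concern.** A chi-square statistic has no covariates, so the adjusted result must come from some other model, and the text does not fix which. The possible readings differ greatly in what they deliver. One has no estimable arm effect, one has an estimable effect with a badly inflated type I error, and others are sound. The sound ones are either conditional on univariate findings (mixed models) or run as an addition with no stated precedence (the cluster-level analysis). The trial is unblinded, its outcome is reported by nurses, and only eight units were randomised. Leaving the model to be chosen after the univariate results are seen adds a further source of error on the primary result.

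**Working it through.** **Inputs from the protocol article.** 8 centres, 4 per arm, 4 pairs; m = 600 punctures per centre per period; two-sided 5%; planning rates 9.3% and 4.65%, mean (9.3 + 4.65)/2 ≈ 7%.

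**Assumptions, because the article gives no values.** ICC 0.005 to 0.02; cluster autocorrelation (CAC, the correlation of a centre's true rates across the two periods) 0.5 to 0.9.

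**1. Is the arm effect estimable?** Rank of the design matrix:

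| Model | Columns | Rank | Arm effect |
|---|---|---|---|
| Post-training: 8 fixed centres + arm | 9 | 8 | not estimable |
| Both periods: centres + period + arm | 10 | 9 | not estimable |
| Both periods: centres + period + arm-by-period | 10 | 10 | estimable |
| Post-training: 4 pairs + arm | 5 | 5 | estimable |

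A random centre effect also leaves arm estimable.

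**2. Type I error of the chi-square.** The variance is understated by 1 + (m − 1) × ICC. At ICC 0.01 this is 1 + 599 × 0.01 = 6.99. The actual error is 2 × P(Z > 1.96/√6.99) = 2 × P(Z > 0.741) ≈ 46%.

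**3. Type I error of the fixed-centre pre/post model on punctures.** Fixed centre effects remove the stable part of the centre variance but not the part that changes between periods. The understatement is 1 + m × ICC × (1 − CAC)/(1 − ICC).

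| ICC | CAC | Factor | Type I error |
|---|---|---|---|
| 0.01 | 0.9 | 1.61 | 12% |
| 0.01 | 0.8 | 2.21 | 19% |
| 0.01 | 0.5 | 4.03 | 33% |
| 0.02 | 0.9 | 2.22 | 19% |
| 0.02 | 0.8 | 3.45 | 29% |
| 0.02 | 0.5 | 7.12 | 46% |

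Simulation at a 7% event rate with 20,000 trials per setting agrees to within about one percentage point. A t-test on the eight centre changes stays at about 5%. So does a regression of the eight post-training rates on arm and baseline rate.

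**4. What the baseline data buy with eight centres.** The pre/post correlation of observed centre rates is r = CAC × ICC/(ICC + (1 − ICC)/600). In large samples the variance factor is 1 − r². Here the slope is estimated from 6 within-arm degrees of freedom, which multiplies the variance by 1 + 1/(6 − 2) = 1.25.

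| ICC | CAC | r | 1 − r² | × 1.25 |
|---|---|---|---|---|
| 0.005 | 0.5 | 0.375 | 0.86 | 1.07 |
| 0.01 | 0.5 | 0.429 | 0.82 | 1.02 |
| 0.02 | 0.5 | 0.462 | 0.79 | 0.98 |
| 0.005 | 0.8 | 0.601 | 0.64 | 0.80 |
| 0.01 | 0.8 | 0.687 | 0.53 | 0.66 |
| 0.02 | 0.8 | 0.740 | 0.45 | 0.57 |

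The variance therefore changes by between about +8% (simulated; +7% by formula) and −43%. The critical t also rises from 2.45 (6 df) to 2.57 (5 df), a further factor of (2.57/2.45)² ≈ 1.10 on squared interval width. At CAC 0.5 the adjustment is then a net loss.

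**5. What keeping the pairs costs.** A paired test has 3 df and critical t 3.18. A within-pair permutation test cannot go below p = 2/2⁴ = 0.125; with the pairs broken the minimum is 2/70 = 0.029. Arm, baseline rate and pair together leave 8 − 6 = 2 df, critical t 4.30.

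**The case against.** The strongest reply is that the article never says centre is a fixed effect or that only post-training data are used. It names mixed models, it lists baseline next to centre, and it holds baseline data for every centre. Fixed or random is a detail an analysis plan usually settles. A cluster-level analysis is promised as well, and the guide it cites is not at hand, so it cannot be ruled out that the guide covers pairing or baseline.

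Much of this stands. A reader might infer that the centre adjustment is aliased with arm in every form. It is not: the aliasing is confined to fixed centre terms without an arm-by-period term. A reader might also infer that no valid analysis is planned; the additional cluster-level analysis could be one. The 12% to 46% range belongs to one reading of an open sentence, not to a model the article has adopted.

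What does not stand is that this is mere missing detail. The article names the deciding test, says its result will be adjusted, makes mixed models depend on univariate findings, and places the cluster-level analysis second. These are choices the text has made, and an analysis plan that followed them would inherit the problem.

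**Conclusion.** The point holds in a limited form and needs correcting, because it concerns the primary result. As written, the adjustment is not an executable analysis. With a fixed centre term on post-training data there is no arm effect to estimate. With a fixed-centre pre/post model that ignores centre-by-period variation, type I error is about 12% to 33% at ICC 0.01 and 19% to 46% at ICC 0.02. The unadjusted chi-square is at about 46% for ICC 0.01. All these figures rest on assumed ICC and autocorrelation values. The added error from univariate screening is real in principle but cannot be sized from the article.

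Two further inferences are not supported. The absence of the pairs from the analysis is not shown to be an error: an unpaired centre-level analysis is generally valid and tends to be conservative when matching works. Nor is baseline adjustment a free gain. The large-sample factor suggests variance reductions of 14% to 55% for these inputs, but with eight centres the benefit appears only when the pre/post correlation is high.

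**What to change.** Replace the adjustment sentence in {20a} and {20b} with one decisive analysis, chosen now from two:

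- regression of the eight post-training (T8) centre rates on arm and baseline (T5) centre rate, tested on 5 df; or
- a mixed model on T5 and T8 punctures with an arm-by-period effect, random centre, random centre-by-period, nurse experience as a named covariate, and a named small-sample degrees-of-freedom method.

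Make the chi-square descriptive. Delete the fixed-centre adjustment and the rule that lets univariate results decide on multivariable models. State in advance whether the matched pairs are kept or broken. Pair strata are not required, given the 3 df that four pairs leave.

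**Cost.** Wording only; no new data. Intervals will be wider and degrees of freedom fewer than the puncture-level test suggests. The baseline term lowers the variance by roughly 20% to 43% at autocorrelation 0.8 but brings no gain, or a small loss, at about 0.5. The choice should therefore be made on prior grounds, not after seeing the data.
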